**Background**

Fluid therapy is probably the most ubiquitous therapeutic intervention in critically ill patients, particularly in those suffering from sepsis (1, 2). Despite this, many aspects of the intervention remain subjects of controversy. There is an ongoing discussion regarding what fluid to give, how much to give and when to give it. Furthermore, while short term goals are to improve cardiac output, systemic blood pressure and organ perfusion, the long term hemodynamic effects are not well described. Excess fluids in the intensive care unit (ICU) has been associated with increased long term morbidity (3-6). In addition, recent trials have shown potential harm due to fluid administration with an increase in mortality in pediatric septic patients in Africa (7, 8). The hemodynamic effects of fluid boluses are small and short lived (9, 10). Since fluids are currently being given in large volumes to critically ill patients in the stabilization phase without a full understanding of their physiological effects, further research in this field could have potential benefit for large numbers of patients who are at high risk of dying.

**Aim**

The aim is to investigate to what extent the expectations of the attending physician concerning hemodynamic effects from the infused fluid in the critically ill are met.

Primary outcome: To describe the accuracy and precision of the expectations of the clinicians of the effect of a fluid bolus at completion of the fluid bolus. Secondary outcomes: To describe the accuracy and precision of the expectations of the clinicians of the effect of a fluid bolus one hour after the completion of the fluid bolus. The reasons for fluid administration. Changes in hemodynamic variables (Cardiac Index (CI), heart rate, blood pressure, CVP,) and lactate, central/mixed venous saturation (ScvO2/SvO2) and urinary output.

**Methods**

Observational multi-center study of fluid administration in the ICU:s at two Swedish tertiary centers (Södersjukhuset and Danderyds Sjukhus) and one Australian university hospital (Austin Hospital). Planned recruitment of 100 adult patients.

Inclusion criteria: Admission to ICU. Age 18 years or older.

Exclusion criteria: Patients in whom death is considered imminent (within 24 hours). The intensive care physician declines to participate.

Patients will receive standard care at the discretion of the treating physicians, including all measurements and monitoring. When the treating physician chooses to give a fluid bolus (defined as 250 mL or more of fluids over 30 minutes or less), the patient will be included and the physician asked to fill out a questionnaire asking for pre-defined reasons to give fluids: hypotension, tachycardia, oliguria, low central venous pressure (CVP), high lactate levels, low mixed venous oxygen saturation (SvO_2_) or central venous oxygen saturation (ScVO_2_) and low cardiac output (CO). Also, the physician will be asked to specify what hemodynamic response of these variables is expected at completion of the bolus and one hour later. The expectations and results of the first bolus after inclusion will be measured and any further boluses given to the same patient will not lead to re-inclusion and further questionnaire’s. The first bolus after inclusion will be studied, which can be at any time during the ICU-stay. For comparison, data will be extracted from the departmental documentation system (Clinisoft^®^, TakeCare^®^ or other methods) regarding MAP, pulse rate, CO, CVP, urine output and pertinent laboratory values such as lactate, SvO_2_ or ScVO_2_ and creatinine. Measurements will be registered before the onset of the fluid bolus and until 60 min after completion of the fluid bolus. If any other static or dynamic hemodynamic variables such as Pulse Pressure Variation (PPV), Stroke Volume Variation (SVV), Extravascular Lung Water (EVLW) or Stroke Volume Index (SVI) are being measured this data will be extracted as well. Any infusions of vasoactive medications and diuretics given will also be recorded and dosages registered will be accounted for as confounders for hemodynamic changes. Any fluids administered during the study period of besides those of the fluid bolus that led to inclusion will be recorded and accounted for as confounders. Fluids will be registered as colloids, crystalloids or maintenance fluids. For MAP, pulse rate and any hemodynamic variables values will be recorded according to the sampling in the electronic system. Laboratory values will be ordered at the clinicians’ discretions as usual (usually at admission and then as indicated clinically) and extracted at these intervals. Urine output will be recorded for six hours following the fluid bolus.

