**Statistical analysis**

The accuracy of the physicians’ estimations of the effect of a fluid bolus will be described using Bland-Altman methodology. In addition, clinicians’ ability to predict the hemodynamic response will be assessed by calculating sensitivity, specificity, PPV, NPV and the area under the receiver operating characteristics curve. Outcomes will be compared after log transformation where appropriate. Comparisons will be made using t-test and ANOVA for repeated-measures or Wilcoxon signed-rank test and Kruskal-Wallis test according to the underlying distribution for continuous data and Fishers’s exact test for categorical data. Multiple regression analysis will also be performed adjusting for predefined confounding factors associated with hemodynamic changes: change in vasopressors, sedatives, diuretics, change in pacemaker rhythm, additional fluid boluses.

Ethical considerations

Ethical approval will be sought from the Ethical Review Board of Stockholm and the Austin ethical review board.

Information will be posted on the study sites, and if objections are raised to inclusion patients will not be included.

Patients in Stockholm will be covered by Sweden’s Patient Insurance policy.

Data collected will be coded and treated confidentially

The study will be observational and no changes will be made in the care of the patients included. There are no foreseeable risks for the patients to be included in this study.

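### Physicians' predictions are what is judged, but repetition is limited only by patient, so repeat predictions by one physician are neither capped nor identifiable from the listed data

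*Protocol*

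**What the plan says.** The Aim section asks "to what extent the expectations of the attending physician concerning hemodynamic effects" are met, and the primary outcome is "To describe the accuracy and precision of the expectations of the clinicians of the effect of a fluid bolus at completion of the fluid bolus". The thing measured is therefore a physician's prediction, set against what then happens to the patient.

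The Methods section gives "Planned recruitment of 100 adult patients" at two Swedish centres and one Australian centre. The section on preliminary results places the study in autumn 2017. When a treating physician decides on a bolus, "the patient will be included and the physician asked to fill out a questionnaire". Only the first bolus per patient is studied, and "any further boluses given to the same patient will not lead to re-inclusion". The only rule at physician level is the exclusion "The intensive care physician declines to participate".

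Under Statistical analysis, the accuracy of the estimates "of the effect of a fluid bolus will be described using Bland-Altman methodology". The section adds sensitivity, specificity, predictive values and AUC, then t-tests, repeated-measures ANOVA, rank tests and Fisher's exact test, and a multiple regression. The regression's predefined confounders are vasopressor changes, sedatives, diuretics, pacemaker rhythm changes and additional boluses. Neither physician nor centre is among them, and clustering is not mentioned.

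**The concern.** The protocol guards against repetition in the patient, but the quantity of interest belongs to the physician. A physician who tends to overestimate the effect of fluid may do so on every questionnaire. Predictions from that physician then carry less information than the same number from different physicians.

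Three things are at stake:

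- **Precision of the bias.** An interval for the mean difference between expected and observed response, computed as if there were 100 independent predictions, would be too narrow. The same applies to p-values and to intervals for sensitivity, specificity, AUC and regression coefficients.
- **Weight.** A few physicians with many questionnaires could count heavily in the overall answer, and the listed data would not show it.
- **Recoverability.** An analysis plan can add a clustered method later. It cannot do so if nobody recorded who made each prediction. That makes the identifier a matter for the protocol.

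Repeated-measures ANOVA and the signed-rank test do not solve this. They deal with repeated or paired values, not with different patients who share a physician.

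**Working it through.** **The plan's own figure.** The 100 patients cannot be re-derived, because the protocol gives no alpha, power, SD or target precision. The check therefore takes N = 100 as given and asks what clustering would do to it.

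**Inputs.** From the protocol: N = 100, three centres, one prediction per patient. Assumed, because the protocol gives neither: 50 or 20 physicians, and an intraclass correlation (ICC) of 0.1 or 0.2 for errors by the same physician. Differences are expressed in units of their total SD.

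**Reference under independence.** The 95% half-width for the bias is 1.96/√100 = 0.196 SD. For a limit of agreement it is 1.96 × √(1/100 + 1.96²/(2 × 99)) = 0.336 SD.

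**Equal caseloads.** With m predictions per physician:

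- design effect DE = 1 + (m − 1) × ICC
- effective N = 100/DE
- correct half-width = 0.196 × √DE
- coverage of the standard 95% interval ≈ 2Φ(1.96/√DE) − 1

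Example with 20 physicians (m = 5) and ICC 0.2: DE = 1 + 4 × 0.2 = 1.8, effective N = 100/1.8 = 56, half-width = 0.196 × 1.34 = 0.263 SD, coverage = 2Φ(1.461) − 1 = 85.6%.

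**Unequal caseloads.** DE = 1 + (Σmᵢ²/N − 1) × ICC, where mᵢ is the number of predictions from physician i. Caseload shares were drawn from a Dirichlet distribution with parameter 2, which is also an assumption. For 20 physicians the expected sum of squared shares is 20 × (2 × 3)/(40 × 41) = 0.0732. The expected Σmᵢ²/N is then (100 + 100 × 99 × 0.0732)/100 = 8.24. So DE = 1 + 7.24 × 0.1 = 1.72 at ICC 0.1, and 1 + 7.24 × 0.2 = 2.45 at ICC 0.2.

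| Scenario | ICC | DE | Effective N | Coverage of standard 95% interval for the bias |
|---|---|---|---|---|
| One prediction per physician, or ICC = 0 | – | 1.0 | 100 | 95% |
| 50 physicians, equal | 0.1 | 1.1 | 91 | 94% |
| 50 physicians, equal | 0.2 | 1.2 | 83 | 93% |
| 20 physicians, equal | 0.1 | 1.4 | 71 | 90% |
| 20 physicians, equal | 0.2 | 1.8 | 56 | 86% |
| 20 physicians, unequal | 0.1 | 1.72 | 58 | 87% |
| 20 physicians, unequal | 0.2 | 2.45 | 41 | 79% |

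**Simulation.** Repeated simulations agree with the formula. With 20 physicians and equal caseloads they gave about 90% to 91% at ICC 0.1 and 85% to 86% at ICC 0.2. With unequal caseloads they gave 86% to 87% and 78% to 79%. In that unequal scenario the two busiest physicians supplied on average 27 of the 100 predictions.

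**Limits of agreement.** Ignoring physicians, the expected sample variance is the true total variance times (N − DE)/(N − 1). At DE = 1.8 this is 98.2/99 = 0.992, so the SD is about 0.4% too small. In the simulations, with 50, 20 or 10 physicians and equal caseloads, the mean SD was 0.987 to 0.997 of the true value. The limits themselves hardly move. Their intervals suffer less than that of the bias: with 20 physicians, equal caseloads and ICC 0.2, coverage for the upper limit was about 90%.

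**The case against.** A reader might infer that the plan analyses all 100 predictions as independent and that its confidence intervals are therefore too narrow. The documents do not support that. The Statistical analysis section names families of methods and is silent on error structure. It specifies no confidence interval. Bland-Altman analysis has versions for clustered data, regression can carry random effects or robust errors, and an analysis plan that is not shown may set these. Narrowing also needs both repeat physicians and a positive correlation, and the protocol quantifies neither.

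The missing identifier is also not proof that none will be collected. The data list in Methods is not exhaustive: sedatives and pacemaker rhythm are adjusted for in the analysis but do not appear there. The questionnaire itself is not shown.

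Finally, the primary outcome is descriptive, with no primary hypothesis test, and the limits of agreement barely change as point estimates. With 50 physicians and equal caseloads the loss of coverage is only one or two percentage points.

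All of this stands, and it makes the consequence conditional. It does not remove the gap. The protocol thought about repetition and closed it only for patients, although physicians' expectations are the outcome. Whether physicians may repeat, and whether they can be told apart, concerns inclusion and data collection. A later analysis plan cannot repair that if the identifier was never recorded.

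**Conclusion.** The point holds in conditional form. The protocol neither caps nor identifies repeat predictions by the same physician, and the methods it names assume independent predictions in standard form. If physicians contribute repeatedly and their errors correlate, standard intervals and p-values will be too optimistic. Repeats are plausible with 100 boluses at three ICUs in one season.

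The size runs from nothing (one prediction each, or no correlation), through nearly negligible (94% and 93% coverage with 50 physicians), to material (90% and 86% with 20 physicians and equal caseloads, 87% and 79% with unequal caseloads). These figures rest on assumed physician numbers, ICCs of 0.1 and 0.2, and an assumed spread of caseloads. The protocol does not show which scenario applies. The estimated limits of agreement are little affected. Nor does the protocol make variation between physicians an outcome in its own right, although separating it from patient variation would help to interpret the precision that the primary outcome promises.

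**What to change.** - Add a coded physician ID to each questionnaire and list it among the data collected.
- Report the number of physicians and the distribution of predictions per physician, overall and by centre.
- Estimate the bias and limits of agreement from a model with a physician random effect, building the limits from total variance (between plus within physician).
- Use physician-cluster bootstrap or cluster-robust intervals for sensitivity, specificity, AUC and the regression coefficients. With few physicians, a small-sample correction is advisable.
- Consider centre as a further term. Whether it enters as a fixed effect is a matter of preference with three sites.

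The cost is one coded field and a slightly more elaborate analysis. Intervals will be somewhat wider if the correlation is real: with 20 physicians and equal caseloads the interval for the bias widens by √1.4 = 1.18 at ICC 0.1 and √1.8 = 1.34 at ICC 0.2. If each physician contributes once, or there is no correlation, the results will hardly differ from the standard ones. The ID has to be in place before data collection; the modelling detail can go in the analysis plan.

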**Statistical analysis**

The accuracy of the physicians’ estimations of the effect of a fluid bolus will be described using Bland-Altman methodology. In addition, clinicians’ ability to predict the hemodynamic response will be assessed by calculating sensitivity, specificity, PPV, NPV and the area under the receiver operating characteristics curve. Outcomes will be compared after log transformation where appropriate. Comparisons will be made using t-test and ANOVA for repeated-measures or Wilcoxon signed-rank test and Kruskal-Wallis test according to the underlying distribution for continuous data and Fishers’s exact test for categorical data. Multiple regression analysis will also be performed adjusting for predefined confounding factors associated with hemodynamic changes: change in vasopressors, sedatives, diuretics, change in pacemaker rhythm, additional fluid boluses.

Ethical considerations

Ethical approval will be sought from the Ethical Review Board of Stockholm and the Austin ethical review board.

Information will be posted on the study sites, and if objections are raised to inclusion patients will not be included.

Patients in Stockholm will be covered by Sweden’s Patient Insurance policy.

Data collected will be coded and treated confidentially

The study will be observational and no changes will be made in the care of the patients included. There are no foreseeable risks for the patients to be included in this study.

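### Bland-Altman is the only method named for the numeric accuracy of expectations; its usual plot tilts even for calibrated forecasts, so a calibration analysis should sit beside it.

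*Protocol*

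**What the plan says.** The Aim section sets the primary outcome: "To describe the accuracy and precision of the expectations of the clinicians of the effect of a fluid bolus at completion". A secondary outcome asks the same one hour later.

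Under Methods, "the physician will be asked to specify what hemodynamic response of these variables is expected at completion of the bolus and one hour later". The actual changes are extracted afterwards from the departmental records. The pair under comparison is therefore a prior forecast and a later observation. Methods also gives the size: "Planned recruitment of 100 adult patients", with one bolus studied in each.

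Under Statistical analysis, the correctness of the estimates "of the effect of a fluid bolus will be described using Bland-Altman methodology". The next sentence adds that the clinicians' "ability to predict the hemodynamic response will be assessed by calculating sensitivity, specificity, PPV, NPV and the area under the receiver operating characteristics curve". Neither sentence is tied to the primary or a secondary outcome. A multiple regression is also planned, but it is described as adjustment for confounders of hemodynamic change, not as a regression of observed on expected change. The protocol names no horizontal axis for the plot, no test for trend and no calibration analysis.

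**The concern.** Bland-Altman was built for two measurements of the same quantity. A forecast is a different kind of quantity. If it is right on average, the observed change equals the forecast plus whatever could not be foreseen, so forecasts must vary less than outcomes unless prediction is perfect. In the usual plot of difference against mean, that gap in variance alone produces a slope.

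A reader could then conclude that physicians under-predict large responses and over-predict small ones when each forecast is in fact right on average. The summary figures have a related weakness. A mean bias of zero is also what someone with no skill obtains by naming the average every time. Wide limits cannot be attributed to poor forecasting or to patient variability unless the spread of the observed changes is shown next to them. What is at stake is the interpretation of the primary outcome.

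**Working it through.** **Inputs.** From the protocol: a forecast and an observed change for each patient (Methods), Bland-Altman as the method (Statistical analysis), and n = 100 (Methods). The protocol states no SDs, correlation or R², so there is no figure of its own to reproduce and a range is assumed. It is also assumed that the expectation is recorded as a number, which Bland-Altman requires.

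**Notation.** F is the forecast, Y the observed change, D = F - Y and M = (F + Y)/2.

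**Step 1: source of the tilt.** cov(D, M) = (Var F - Var Y)/2. It is zero only when the variances are equal.

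**Step 2: calibrated forecasts.** Let Y = F + e with e uncorrelated with F, Var Y = 1, Var F = R² and Var e = 1 - R². Then:

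- corr(D, M) = -(√(1 - R²)/2) / √(R² + (1 - R²)/4)
- slope of D on M = -((1 - R²)/2) / (R² + (1 - R²)/4)
- half-width of the limits = 1.96 √(1 - R²) SD(Y)
- slope of Y on F = 1 at every R² above 0

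The AUROC, for a response above the mean, comes from simulation with 200,000 draws.

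| R² | corr(D, M) | slope of D on M | half-width / SD(Y) | AUROC |
|---|---|---|---|---|
| 0.1 | -0.83 | -1.39 | 1.86 | 0.64 |
| 0.2 | -0.71 | -1.00 | 1.75 | 0.70 |
| 0.5 | -0.45 | -0.40 | 1.39 | 0.83 |
| 0.9 | -0.16 | -0.05 | 0.62 | 0.97 |

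**Step 3: forecasts with no skill.** Let F be independent of Y, with the right mean and SD(F) = k SD(Y). The bias is 0 for every k. The half-width is 1.96 √(1 + k²) SD(Y) and the slope of D on M is 2(k² - 1)/(k² + 1).

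- k = 0 (same number for everyone): half-width 1.96 SD(Y), slope -2.0
- k = 0.5: half-width 2.19 SD(Y), slope -1.2
- k = 1: half-width 2.77 SD(Y), slope 0

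A flat plot is thus no proof of good forecasts, since k = 1 gives one with no skill at all. Calibrated forecasts with R² = 0.2 have limits narrower than the constant forecast by 1 - √0.8 = 0.106, about 11%.

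**Step 4: an example in mmHg.** Assume SD 5 for the expected and 10 for the observed change in MAP, with correlation r.

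- r = 0.5: calibration slope = 0.5 × 10/5 = 1.0. SD(D) = √(25 + 100 - 50) = 8.66, so limits are bias ± 17.0. corr(D, M) = -75/√(125² - 4 × 0.25 × 25 × 100) = -0.65.
- r = 0: SD(D) = √125 = 11.18, so limits are bias ± 21.9. corr(D, M) = -75/125 = -0.60.
- Constant forecast: limits are bias ± 1.96 × 10 = ± 19.6.

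Calibrated forecasters and forecasters with no skill produce nearly the same tilt.

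**Step 5: precision of the remedy.** For a calibrated forecast, SE(slope of Y on F) = √[(1 - R²)/(R²(n - 2))]. With all 100 patients and R² = 0.2 this is √(0.8/19.6) = 0.20, a 95% half-width of about 0.40. It widens as fewer patients have the variable measured.

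**The case against.** The case for leaving the plan alone has several sound parts.

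- **Bland-Altman suits the outcome as worded.** Mean bias describes accuracy and the limits describe precision. Neither depends on the horizontal axis. If patient variability makes the limits wide, expectations were still not met, and that answers the stated aim. This stands, and it is why both summaries should stay.
- **Other methods are planned.** A reader might infer that Bland-Altman is the only method for the primary outcome, or that nothing in the plan has a no-skill reference. The document does not support either. The discrimination measures follow in the next sentence and are not confined to a secondary outcome, and AUROC has its own no-skill value of 0.5. But AUROC depends on ranks alone: doubling or halving every expected change leaves it unchanged. It cannot show whether the stated sizes are right. Sensitivity, specificity and predictive values register size only where it crosses a cut-off.
- **The tilt is not always strong.** A reader might infer that calibrated physicians are bound to show marked proportional bias. With no SDs or R² in the protocol that cannot be said. At R² = 0.9 the correlation is only about -0.16, and with equal variances there is no tilt.
- **No trend test or axis is specified, and an unseen SAP may add detail.** The first part stands, so this is a risk of misinterpretation and not a wrong test. The second does not dispose of the point: the protocol itself selects an agreement method for a forecast-outcome pair, and the remedy improves that stated choice.

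**Conclusion.** The point holds as a cheap improvement to the stated method, not as an error that invalidates the primary outcome. Bland-Altman is the only method named for the numeric accuracy of the expectations, and its usual plot cannot separate calibrated forecasting from poor forecasting. For calibrated forecasts the artefactual correlation runs from about -0.83 at R² = 0.1 to -0.16 at R² = 0.9. It is substantial for R² up to about 0.5 and minor near 0.9. These values rest on an assumed range, on numeric expectations and on the difference being plotted against the mean, as is usual.

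Mean bias and limits remain valid descriptions of how far observed changes departed from expected ones. Read alone they say little about skill, since zero bias is compatible with none and modest skill (R² = 0.2) narrows the limits by only about 11%.

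**What to change.** Three changes, for each variable with a numeric expectation, at bolus completion and at one hour:

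1. Keep mean bias and limits of agreement, but plot observed minus expected change against the expected value. For calibrated forecasts this plot has no trend, because the error is uncorrelated with the forecast.
2. Report the regression of observed on expected change, giving the intercept and slope with 95% CIs. Calibration corresponds to intercept 0 and slope 1.
3. Report the SD of observed change beside the SD of forecast errors, as the benchmark for naming the average for everyone.

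Keep the planned discrimination measures alongside.

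The cost is a little extra analysis, with no new data collection and no change to care. The one drawback is imprecision: the slope's 95% half-width is about 0.40 at R² = 0.2 even with all 100 patients, and will be larger for rarely measured variables. For those, the interval should be read as the limit of what the data can say.

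### Kruskal-Wallis, a test for independent groups, is named as the rank-based counterpart of repeated-measures ANOVA for serial values on the same patients

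*Protocol*

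**What the plan says.** The Statistical analysis section of the protocol chooses tests for continuous data by distribution: "t-test and ANOVA for repeated-measures or Wilcoxon signed-rank test and Kruskal-Wallis test according to the underlying distribution for continuous data". The first pair is parametric and the second rank-based. By position, the t-test corresponds to the signed-rank test and repeated-measures ANOVA to Kruskal-Wallis.

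The Methods section sets the data structure. The sample is a single cohort ("Planned recruitment of 100 adult patients"), with one studied bolus each, since "any further boluses given to the same patient will not lead to re-inclusion". On timing, "Measurements will be registered before the onset of the fluid bolus and until 60 min after completion of the fluid bolus", and physicians state "what hemodynamic response of these variables is expected at completion of the bolus and one hour later". With the baseline value, this gives three key time points per patient.

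The outcome concerned is secondary. The Aim section lists "Changes in hemodynamic variables (Cardiac Index (CI), heart rate, blood pressure, CVP" and further variables there. The primary outcome is descriptive: "To describe the accuracy and precision of the expectations of the clinicians of the effect of a fluid bolus at completion of the fluid bolus". It is analysed by Bland-Altman methods.

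**The concern.** Kruskal-Wallis treats the values at the three times as if they came from three separate sets of patients. Because each patient contributes to all three, differences between patients, which cancel in a within-patient comparison, stay in the test as noise. The p-values then come out too large.

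The risk is a missed change. A real shift over the hour after the bolus could be reported as no change, and change over time is what this secondary outcome is meant to describe. The Background section expects bolus effects to be modest and brief, and modest shifts are where the loss can be greatest.

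**Working it through.** **Inputs from the protocol.** 100 patients (Methods); one bolus per patient, so patients are independent of one another (Methods); three key times: before, completion, one hour (Methods).

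**Inputs assumed.** The protocol gives no within-patient correlation, effect size, SD or significance level, so it has no figure to reproduce. Assumed: two-sided 0.05; the same correlation rho between any two times, varied from 0 to 0.9; mean shifts of 0, d and d/2 SD at the three times, with d from 0 to 0.5; complete data.

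**Step 1: type I error by formula.** With no true change, the Kruskal-Wallis statistic for three equally correlated time points behaves approximately like (1 − r) times a chi-square variable with 2 degrees of freedom, where r is the rank correlation between two times. For normal data r = (6/π)·arcsin(rho/2). Since P(chi-square with 2 df > x) = exp(−x/2), the true level is 0.05 raised to the power 1/(1 − r).

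- rho 0.3: r = 0.288, 1/(1 − r) = 1.404, level = 0.05^1.404 = 0.015
- rho 0.5: r = 0.483, 1/(1 − r) = 1.933, level = 0.05^1.933 = 0.003
- rho 0.7: r = 0.683, 1/(1 − r) = 3.154, level = 0.05^3.154 = 0.00008
- rho 0.85: r = 0.838, 1/(1 − r) = 6.186, level below 0.0000001

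**Step 2: simulation, 4,000 runs per setting.**

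| rho | d (SD) | Kruskal-Wallis | Friedman |
|---|---|---|---|
| 0 | 0 | 0.054 | 0.053 |
| 0.3 | 0 | 0.015 | 0.052 |
| 0.5 | 0 | 0.003 | 0.054 |
| 0.7 | 0 | 0.000 | 0.048 |
| 0.3 | 0.3 | 0.40 | 0.46 |
| 0.3 | 0.5 | 0.92 | 0.90 |
| 0.5 | 0.3 | 0.35 | 0.61 |
| 0.5 | 0.5 | 0.93 | 0.97 |
| 0.7 | 0.2 | 0.05 | 0.49 |
| 0.7 | 0.3 | 0.29 | 0.85 |
| 0.7 | 0.5 | 0.96 | 1.00 |
| 0.9 | 0.2 | 0.003 | 0.93 |

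Rows with d = 0 show type I error; the others show power. The type I errors agree with the formula. A repeat with a different random seed gave 0.30 versus 0.84 at rho 0.7 and d 0.3, so the second decimal is simulation noise.

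**Step 3: does the normal model matter?** The rank route is meant for non-normal data. Both tests use only ranks, so one increasing transformation applied to all values leaves both p-values unchanged. Exponentiating simulated data to a log-normal shape changed no p-value. The table therefore also covers skewed data of that kind, with the shift read on the log scale. It does not cover every non-normal shape.

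**The case against.** **Kruskal-Wallis may be meant for independent groups.** There are three sites and several reasons for a bolus, and the test would be valid for comparing them. But the text does not limit it to that use. It sets the test beside repeated-measures ANOVA and next to the signed-rank test, itself a paired test. On the kinder reading, no rank-based test is named for three or more repeated values, so the sentence needs correction either way.

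**The rank route may seldom be used.** The section provides for log transformation where suitable, so skewed variables such as lactate may remain under repeated-measures ANOVA, which fits the design. Laboratory values are taken at clinicians' discretion and urine output is followed for six hours, so neither need form the three-point series simulated here. This stands. It narrows the reach of the error, mainly to monitored variables such as pressure, heart rate and CVP, without making the rule right.

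**Friedman is not always better.** At rho 0 it has less power (0.34 versus 0.44 at d 0.3), and it drops any patient with a missing time point. This also stands and is the reason to offer a mixed model.

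A reader might go further in two ways that the protocol does not support:

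- *That Fisher's test is misapplied to paired data.* The text says only "exact test for categorical data" and names no paired categorical comparison. Expected versus observed response already has sensitivity, specificity, predictive values and ROC area, and Fisher's test is suitable between patients.
- *That most of the power is lost.* This is true only for small shifts with high correlation, and the protocol gives neither figure.

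**Conclusion.** Wrong as written; should be fixed. The rank-based test named for three or more repeated measurements does not match a design in which every patient supplies all time points. The mismatch in type I error appears at every positive correlation examined: about 0.015 at rho 0.3, 0.003 at rho 0.5 and effectively zero from 0.7 upwards, against about 0.05 for Friedman. The power cost depends on unknown quantities: negligible at rho 0.3 or for 0.5 SD shifts, moderate at rho 0.5 with a 0.3 SD shift, large at rho 0.7 or more with shifts of 0.2 to 0.3 SD.

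The consequence is limited. It arises only when the rank route is taken across three or more times, concerns a secondary outcome, and can hide a change but does not create false positives. The primary analysis uses neither test, and two-point comparisons use the signed-rank test, which is correctly paired. That is why the point does not rank as essential. The sizes rest on the assumed correlations and shifts, equal correlation between times, and complete data from 100 patients; fewer complete series would lower power for both tests.

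**What to change.** In the Statistical analysis section, for comparisons across time points within patients, replace Kruskal-Wallis with the Friedman test. Where some time points are missing, use instead a mixed model with a patient random effect, on a transformed scale if needed, so that patients with incomplete series are kept. State that Kruskal-Wallis is reserved for comparisons between independent groups of patients, such as sites.

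The cost is one or two sentences. No extra data, patients or measurements are needed, and the primary analysis does not change.
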